## 10. Study treatments

### 10.1 PASTA pathway (intervention group)

Patients in the intervention group will undergo assessment by a paramedic who has received specific training and holds study documentation supporting the PASTA pathway. A summary of the PASTA pathway is shown in figure 1. It consists of the following stages:

**i. Information:** The paramedic will seek additional information at the scene which is routinely considered during thrombolysis treatment decisions, but is typically not obtained until after hospital admission. This will include:

- The presence of language (i.e. dysphasia) or visual (i.e. visuospatial) problems during a simple clinical examination, which may indicate a level of stroke severity more likely to be considered for thrombolysis treatment than FAST symptoms alone.
- Prescription of anticoagulant medication which would require additional urgent measurement of blood clotting indices before a thrombolysis decision could be made. This medication is also an additional indication for urgent brain imaging by itself, as a stroke due to haemorrhage would trigger urgent reversal its effects.
- A recent medical history of surgery or bleeding which might exclude thrombolysis treatment because of an increased risk of uncontrollable haemorrhage.
- Any previous medical history of transient ischaemic attack (TIA) or stroke, which could assist interpretation of brain imaging and specialist evaluation of the risk versus benefit of thrombolysis treatment.
- The current level of dependency according to whether the patient requires direct assistance with feeding or walking, in order to judge the value of administering thrombolysis treatment relative to the effects of the new stroke.

Within the pathway these information categories will be prompted by the acronym PASTA which represents: Plus dysphasia or visuospatial impairment; Anticoagulant medications; Surgery or other bleeding recently; TIA or stroke previously; Assistance needed daily.

**ii. Pre-notification:** During emergency transfer the paramedic will always be expected to attempt a pre-alert to the destination hospital in accordance with existing local arrangements. Although pre-notification is already a component of standard care, compliance is variable. Existing arrangements differ within regional ambulance services and individual hospitals e.g. direct telephone contact from paramedic, or via ambulance dispatch to ED or to ASU. The individual hospital response can vary according to the timing of the admission (e.g. the patient may be received by a specialist stroke team during weekday office hours and by ED clinicians at other times). The PASTA pathway does not change local processes but routinely prompts standard pre-notification.

**iii. Handover:** On arrival at the hospital's designated location for stroke admissions, the paramedic will provide a standardised handover of stroke-specific information (FAST, onset time, alertness and PASTA details) to the hospital team, indicating any items which were unavailable at the scene. The paramedic will ask the receiving hospital team whether it is possible to go straight to the CT scan if the radiographer is ready, and will remind them about ideal time targets for scan (<15 minutes) and thrombolysis treatment (<30 minutes). A member of the ambulance crew will assist the team with rapid registration of the patient's details on the hospital patient administration system. Prior to CT scan, a hospital clinician will always confirm that the provisional diagnosis is likely to be stroke within the previous 4 hours. In addition, the paramedic will inform the team about the known location of any relatives in order to facilitate information gathering, communication and treatment decisions. As shown in figure 1, the handover structure can be summarised by the abbreviation "FASTA PASTA CT".

**iv. Scan:** If the CT scan is immediately available, the paramedic will assist with patient transfer to the scan room accompanied by at least one member of the hospital team. It will be a local

decision whether the patient is first transferred onto a hospital trolley but any delays should be minimised.

**v. Assist:** If the CT scan is not immediately available, the hospital team will continue with urgent care of the patient according to the local service protocol and the patient will be transferred onto a hospital trolley. If ambulance service operational conditions are suitable and the hospital team require assistance, the paramedic can assist with the following tasks: insertion of an intravenous cannula if not already inserted, determining the patient's weight from assisting with transfer onto measurement scales or contributing towards a team estimation of weight, and repetition / clarification of clinical information (e.g. repeating the handover to a member of the stroke team). If the scan becomes available within 15 minutes of handover, the paramedic will assist with the patient transfer as above.

**vi. Checklist:** At 15 minutes after handover the paramedic will ask a member of the hospital team to confirm progress with key tasks: the status of the emergency brain scan request (if not yet performed) and stroke specialist review, confirmation of relevant medical history and medications, and ordering blood tests for clotting indices if relevant.

**vii. Feedback:** After completion of the checklist, the paramedic will request feedback from a hospital clinician about the provisional pre-hospital diagnosis of stroke, the estimation of onset time and any other aspect of the assessment process.

**viii Completion:** After seeking the checklist and feedback information the paramedic will complete and sign the study documentation. One copy will be retained at the hospital and a further copy will be returned to the ambulance service. The paramedic will depart as per usual operational procedure. This will be within 15-30 minutes of hospital arrival and therefore compliant with NHS Commissioning Board guidance for ambulance to hospital handover of emergency admissions[23].

The paramedic will record a reason if study documentation is signed before completion of the PASTA pathway. Anticipated reasons are:

- The paramedic is no longer contributing towards the clinical care of the patient.
- A change in the clinical state of the patient making the PASTA pathway no-longer appropriate (further details below).
- A stroke mimic condition is clearly identified during the initial hospital assessment and the hospital team determine that it would no longer be appropriate to continue with a care pathway for suspected stroke (further details below).
- A specific request by the regional ambulance control centre that the ambulance crew should become available for another call due to the pressure on resources.

Figure 1: PASTA pathway

[figure not shown]

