| Primary outcome:    | Proportion of participants receiving intravenous thrombolysis.                                                                                                                                                                                                                                                                                                                                                                                                                                                                                                            |
| Secondary outcomes: | 

• Stroke severity and complications at 24 hrs post thrombolysis

• Inpatient mortality

• Destination at discharge and 90 days

• Dependency at discharge and 90 days

• Assistance required at discharge and 90 days

• Time from emergency call and hospital admission to first brain imaging, thrombolysis, stroke unit admission, formal swallow assessment

• Patient experiences during the intervention pathway

• Professional views of the intervention pathway

 |
| Sample size:        | 1297 participants provide 90% power to detect a 10% difference in the proportion of patients receiving thrombolysis.                                                                                                                                                                                                                                                                                                                                                                                                                                                      |
| Study duration:     | 2.5 Years.                                                                                                                                                                                                                                                                                                                                                                                                                                                                                                                                                                |

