### **6.2 Objectives**

- To determine whether the PASTA pathway improves patient care and outcomes. Primary outcome: proportion of patients receiving intravenous thrombolysis. Secondary outcomes: stroke severity 24 hours after thrombolysis (National Institute of Health Stroke Scale (NIHSS)[21]), complications after thrombolysis, inpatient mortality, discharge destination, discharge dependency (modified Rankin Score (mRS)[22]), assistance at discharge, 90 day dependency (mRS), 90 day destination, assistance at 90 days.
- To describe the impact of the PASTA pathway on time intervals from emergency call and hospital admission to first brain imaging, thrombolysis treatment (if given), ASU admission and formal assessment of swallowing safety.
- To describe the number and subsequent diagnoses of suspected stroke patients who travelled to hospital with a study paramedic but following assessment at hospital were not given a diagnosis of stroke ('stroke mimics').
- To determine the cost-effectiveness of the PASTA pathway relative to standard NHS stroke care.

- To report patient experiences during the PASTA pathway, including confidence in the care process and information received about diagnosis and treatment.
- To report professional views and perspectives (paramedics and hospital staff) of the acceptability and feasibility of the PASTA pathway in the clinical setting.

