### **10.2 Standard stroke care (comparison group)**

Patients in the comparison group will receive standard stroke care as per current local ambulance and hospital clinical protocols, which are reinforced by national clinical guidelines and audit. The study will not provide comparison group paramedics with additional training or documentation to support information collection, clinical communication or processes after hospital arrival.

The local thrombolysis assessment and treatment processes in hospital will not be deliberately altered. It is routine practice that all patients receiving thrombolysis are observed for at least 24 hours and undergo repeat CT brain imaging at 24-48 hours to exclude intracranial haemorrhage. Recognised complications of thrombolysis include allergic reactions (angioedema), extra-cranial haemorrhage and intracranial haemorrhage causing symptomatic neurological deterioration (defined as with an increase in NIHSS  $\geq 4$  points within 36 hrs of thrombolysis associated with parenchymal haemorrhage on repeat brain imaging)[24].

Whether or not they receive thrombolysis, all patients with acute stroke should be admitted to an ASU within 4 hours of hospital arrival in order to receive specialist assessment and care tailored to their individual needs. The overall length of stay in hospital reflects pre-morbid conditions and dependency, stroke severity and subsequent medical complications (e.g. pneumonia, thromboembolism, stroke recurrence), progress during rehabilitation, personal social circumstances and the local availability of services to provide further rehabilitation and care in the community (including generic and stroke-specific early supported discharge teams and community rehabilitation teams).

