#### Day 1 pre-admission data:

Suspected stroke diagnosis (FAST; paramedic judgement of stroke or query stroke)  
Symptom onset or last known to be well time (paramedic judgement)  
Pre-notification of receiving hospital  
Times of 999 call, ambulance on scene, ambulance left scene and hospital arrival  
Involvement of rapid response paramedic: yes/no (intervention group only)  
Time of transfer of care (also called handover) from the paramedic to the hospital team  
Time of paramedic signature of the completed ambulance clinical record  
Time paramedic is clear to respond to another incident

The above data will predominantly be transcribed from the routine ambulance clinical record onto a study specific Case Record Form (CRF) by NHS research support staff or other hospital clinical staff trained to deliver this research project. However, some data items are not contained within the routine ambulance clinical record but held within computerised ambulance service dispatch systems. These data will be obtained directly from the ambulance services. For participants travelling to hospital with an intervention paramedic trained to deliver the PASTA pathway, some of the above data will also be recorded onto a study specific paramedic CRF which will additionally record delivery of the PASTA pathway.

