#### Day 1 post-admission data:

Demographic information (age; gender; pre-stroke mRS)  
Date/time of hospital admission  
First blood pressure reading on admission  
First blood glucose reading on admission (capillary or serum glucose)  
Stroke severity on admission (National Institute of Health Stroke Score)  
Stroke onset or last known to be well time (stroke team judgement)  
Current use of anticoagulant medication  
Previous medical history (stroke; TIA; heart failure; atrial fibrillation; diabetes; hypertension)  
Hospital admission locations (ED; stroke unit; critical care; medical admissions ward, other ward)  
First brain imaging time, modality and result (CT / MRI; infarction/primary intracerebral haemorrhage)  
Thrombolysis treatment decision (yes / no; reason why thrombolysis not administered)  
Date/time of thrombolysis (if received)  
Use of other treatments (reversal of anticoagulation if haemorrhagic stroke; acute blood pressure lowering if haemorrhagic stroke or before intravenous thrombolysis; referral or transfer to neurosurgery; referral or transfer for intra-arterial treatment; use of intra-arterial treatments (yes / no; time of puncture)).  
Entry into another clinical trial on day 1 after admission (yes / no; which one)  
Date and time of admission to first stroke unit  
Date and time of assessment of swallow safety at first hospital

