## 18. Statistical analysis

Analysis is by 'treatment allocated'; that is, primary and secondary efficacy and safety outcomes analyses will all use the study group allocation of the attending paramedic; only paramedics completing the study specific training will be considered as members of the intervention group. Thus, data will be analysed pragmatically according to paramedic group allocation, irrespective of the care process actually experienced by individual participants.

The primary end point measure is the proportion of participants who received intravenous thrombolysis. The primary analysis will compare the proportion of participants who received thrombolysis in the two arms of the study using logistic regression. Models will include various covariates and factors, including (but not limited to) participant age and gender and admission time and date (used to define a covariate to reflect background trends).

Secondary outcomes, including stroke severity 24 hours after thrombolysis (measured by an NIHSS score), inpatient mortality and dependency (modified Rankin Scale), will be analysed by appropriate ordinal and binary regression models, with appropriate adjustment for potential covariates and factors.

To address the second objective (that is, the impact of the intervention on various time intervals related to the emergency call), we will use appropriate statistical models. For time intervals between events which always happen (for instance, emergency call to hospital admission), we will employ linear models (after appropriate transformation), again adjusting for statistically significant covariates and factors; if the distributions of residuals are markedly non-normal, further transformation or bootstrapping will be considered. Residual diagnostics will also be used to identify outliers; identified outliers will be excluded and the analysis recalculated. For events which may or may not happen (for instance, emergency call to thrombolysis), we will analyse outcomes via binary regression models and survival analysis, comparing intervention and control arms using the framework of accelerated life testing; both approaches will again accommodate statistically significant covariates and factors.

Other clinical objectives will be addressed by appropriate descriptive statistical measures.

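### Several secondary intervals start or end at an undefined hospital admission time, which may be a registration time that the PASTA pathway can itself move

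*Protocol*

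**What the plan says.** **Outcomes.** The secondary outcomes in section 4 include "Time from emergency call and hospital admission to first brain imaging, thrombolysis, stroke unit admission, formal swallow assessment". Objective 2 in section 6.2 repeats the two starting points: "time intervals from emergency call and hospital admission to first brain imaging" and the later events. Section 18 also uses admission as an end point, in its example of an interval between events that always occur: "for instance, emergency call to hospital admission".

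**Data items.** Section 13 collects two different times.
- The pre-admission list has "Times of 999 call, ambulance on scene, ambulance left scene and hospital arrival". These items come mainly from the routine ambulance record, and some come from dispatch systems. For intervention participants, some are also written on a study paramedic CRF.
- The post-admission list has "Date/time of hospital admission", transcribed from routine medical records.

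The protocol does not say whether admission means arrival or registration, or how the two times relate.

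**Intervention.** The PASTA handover in section 10.1 includes this task: "A member of the ambulance crew will assist the team with rapid registration of the" patient on the hospital's administration system. Section 10.2 says that comparison paramedics receive no "additional training or documentation to support information collection, clinical communication or processes after hospital arrival".

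**The concern.** A start or end point for comparing randomised arms should be one that the intervention cannot change. Here the pathway acts on a hospital administrative step, and an undefined hospital administrative time anchors part of objective 2. If some sites enter the registration time as the admission time, part of the difference between arms would reflect when the clock started and not how quickly care was given.

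The measures at risk are the in-hospital delays to scan and to needle, which section 5 gives as the reason for developing the pathway. Section 8 adds to the exposure: sites are chosen to cover a range of service designs, so what counts as admission may differ between them.

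**Working it through.** The protocol states no figure for this point, so there is nothing to reproduce. The check is the algebra of a moved clock, followed by its possible size.

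**Notation, for one patient**
- c = time of emergency call
- a = time of hospital arrival
- r = delay from arrival to registration
- e = time of the event (scan, thrombolysis, stroke unit admission, swallow assessment)
- L = mean r in control minus mean r in PASTA, so L > 0 means earlier registration under PASTA

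**If recorded admission is registration (a + r)**
- Admission to event = (e − a) − r. Difference, PASTA minus control = true arrival-based difference + L.
- Call to admission = (a − c) + r. Difference = true call-to-arrival difference − L.
- Call to event = e − c. It does not contain r, so the shift is 0.

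**If recorded admission is arrival (a)**
- r drops out and every shift is 0.

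**Inputs for size**
- Median door-to-treatment time of 54 minutes (section 5, NHS 2014).
- L is not in the protocol. The assumed range is 0 to 10 minutes.

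| L (min, assumed) | Shift in admission-to-event | Share of 54 min | Shift in call-to-admission |
|---|---|---|---|
| 0 | 0 | 0% | 0 |
| 1 | +1 | 1/54 = 1.9% | −1 |
| 2 | +2 | 2/54 = 3.7% | −2 |
| 5 | +5 | 5/54 = 9.3% | −5 |
| 10 | +10 | 10/54 = 18.5% | −10 |

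**Worked cases at L = 5.** A true gain of 5 minutes from arrival shows as −5 + 5 = 0. A true gain of 10 minutes shows as −10 + 5 = −5. Call-to-admission looks 5 minutes shorter although nobody arrived sooner.

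**Opposite sign.** Section 10.1 allows a patient to go straight to CT. If registration is completed only afterwards, r grows for those patients. L then falls and may become negative, admission-to-scan shrinks (for an individual it may be near zero or below), and call-to-admission lengthens. The net sign therefore depends on local practice, which the protocol does not describe.

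**The case against.** **Admission may simply mean arrival.** Section 5 speaks of door-to-scan and door-to-needle time. Sections 10.1, 10.2 and 12 state time standards from arrival, and section 18 pairs the emergency call with admission as events that always happen. This is a fair reading, and under it the bias is zero. It does not settle the matter, because section 13 lists arrival and admission as two items from two sources.

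**A reader might infer that the comparisons are distorted.** The documents do not support that. They nowhere identify admission time with the registration stamp, they give no registration delay, and the net direction is open. Nor do they show that control crews never help with registration: section 10.2 says only that the study gives them no extra training or documentation, and local practice may include such help.

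**The anchor for a secondary interval could be left to the SAP.** A derivation rule could. But the protocol itself names admission as the time origin, so changing it corrects a stated choice and does not fill in missing detail.

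**The exposure is limited.** This stands. Each listed interval is also measured from the emergency call, objective 2 is worded as descriptive, and the primary outcome is a proportion that uses no clock.

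**Arrival may also be recorded differently by arm.** Section 13 has some pre-admission items entered additionally on a paramedic CRF for intervention participants only, and does not say which. This stands too, so the fix must name the source.

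**Conclusion.** The point holds as a weakness in how a time origin is fixed, not as a demonstrated bias. The admission-based intervals in sections 4 and 6.2, and the call-to-admission example in section 18, rest on an undefined hospital-record time that the intervention can move wherever that time is the registration time.

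The shift equals the arm difference in registration delay, minute for minute. Over the assumed 0 to 10 minutes it is 0 to 19% of the 54-minute median. Earlier registration would work against PASTA on admission-to-event intervals and in its favour on call-to-admission; late registration after direct transfer to CT would reverse both. The size rests on two assumptions that the protocol neither confirms nor excludes: that some sites record registration as admission, and that registration timing differs between arms. Intervals from the call to clinical events and the primary outcome do not depend on either. The change is worth making because a time point that precedes registration is already collected in both arms.

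**What to change.** - In sections 4, 6.2 and 18, define time zero for all hospital-based intervals as hospital arrival.
- State that arrival is taken from the same routine ambulance record or dispatch source in both arms, and not from the intervention-only paramedic CRF.
- In section 18, replace the call-to-admission example with emergency call to hospital arrival.
- Keep the hospital admission time and report arrival-to-admission by arm descriptively. This would show whether the pathway moved the stamp.

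The cost is wording, since arrival is already on the section 13 list. The downside is small: hospital-based intervals become less directly comparable with sources that use the hospital admission stamp. If admission was always meant as arrival, the same wording serves as the clarification.
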